Physical activity interventions based on social psychological theory are more effective than atheoretical ones in promoting health-protective behaviour [13]. In addition, interventions are more cost-effective when they have theoretically devised approaches and clearly measurable constructs. A theoretical basis for the intervention components and inclusion of key psychological measures based on theory can demonstrate *how* the intervention works, highlighting the processes by which behaviour change occurs [14]. The Health Action Process Approach (HAPA) [15] stipulates a dual-phase approach to action: a *motivational* phase (i.e. outcome expectancy, risk perception, action self-efficacy and intention) and a *volitional* phase (i.e. maintenance self-efficacy, recovery self-efficacy, action planning, coping planning and action control). According to HAPA, intention is a necessary but insufficient condition for action initiation and persistence. People also need to identify effective volitional self-regulatory strategies to enact their intentions and prevent relapse. The effectiveness of HAPA-based interventions has been demonstrated in multiple populations and contexts and across multiple health behaviours [15–21]. The use of this framework to promote physical activity in people with OA does not appear in the literature. However, HAPA has recently been used to identify six physical activity attributes that are most salient to adults with knee OA [22], which supports this framework in this population.

This report describes the methodology of the ENHANCE trial, a randomised controlled trial to test the effectiveness of the ENHANCE programme for a usual care control group. This study seeks to test the hypothesis that the combination of a targeted exercise prescription with behaviour change counselling based on HAPA will be more effective than usual care in increasing the number of daily steps at all-time points after intervention. Concurrently less pain, improved function and reduced metabolic and cardiovascular risks factors will be recorded.

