## Methods/design

The ENHANCE study is an open two-arm parallel-group randomised controlled trial. This is a superiority trial to determine if there is a clinically relevant difference between exercise and behaviour change counselling versus usual care. The 12-week ENHANCE programme is delivered to trial participants by an accredited exercise physiologist (AEP) in a university exercise physiology clinic. Minimum training at this level is a bachelor’s degree in sports science (kinesiology) and a professional honours qualification (4.5 years total full-time study at a tertiary institution). Data are collected at baseline and 26 weeks, and at 26 weeks post-surgery. A schematic diagram of enrolment is shown in Fig. 1.

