### Setting

The study is conducted in Australia at Launceston, Tasmania. The ENHANCE programme is delivered in an exercise physiology clinic at a major university.

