### Randomisation

After completing all baseline data collection measures, participants are randomised to either the intervention group or the control group. Participants in the intervention group receive evidence-based physical activity guidelines supervised by an AEP for the 12 weeks. In addition, those in the intervention group receive an instructor-developed exercise booklet, along with innovative counselling classes five times directly after their exercise session. Participants in the control group will receive an information sheet with general advice on the benefits of physical activity for adults with OA. Participants in either group may receive relevant concomitant care and interventions.

The randomisation schedule has been prepared by a researcher independent of the research project using a computer-generated random number table. To conceal randomisation, the independent researcher has prepared consecutively numbered, sealed, opaque envelopes, which are kept in a locked location. As ENHANCE is an exercise intervention, blinding of the participants and the researchers who conduct the exercise sessions is not possible. Outcome assessors will not be involved in the delivery of the intervention and will be blinded to group allocations.

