### Primary outcome measure

The primary outcome measure is daily physical activity (daily step count and percentage of day spent in sedentary activities). Participants will wear an activity monitor (activePAL™) for seven consecutive days. Data from the device will be recorded and uploaded to a computer. These data will be averaged over the 7 days of activity to calculate a daily step count. The percentage of the day spent in sedentary activities will also be recorded. This measure will be taken upon entry to the study (test 1), and at approximately 6 months (test 2), and then at 6 months after surgery (test 3).

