### Data analysis

Differences in primary and secondary outcomes between groups will be compared using an intention-to-treat analysis. Once a participant is randomised to a study group, they will be considered a trial participant and analysed according to their allocated group, regardless of missing data for follow-ups or the amount of intervention received. Bivariate relationships will be tested with Pearson or Spearman correlations, independent *t*-tests or Mann–Whitney *U* tests (to examine relationships between the dependent variables and the independent variables) or chi squared tests for categorical variables. Each primary and secondary outcome will be analysed using a two-way repeated-measures analysis of covariance (ANCOVA) to determine differences between groups (exercise versus usual care) and between time points (test 1, test 2 and test 3). In addition, effects of the intervention targeting the psychological HAPA-based constructs on regular exercise is tested along with the key processes (mediation) involved. Data will be analysed with a linear mixed model with condition as between-participants effects and time points as within-participants effects. A path analysis will be used to determine mediation effects. Data analysis will be performed using statistical software STATA (STATA 13, Stata Corp, College Station, TX, USA) and Mplus. Statistical significance is set at *p* < 0.05 for all analyses.

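### Test 2 falls half a year after baseline and the models hold only group and time: if steps are seasonal, year-round entry costs the group comparison some precision, and short or uneven entry shifts the time comparison

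*Protocol article*

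**What the plan says.** Methods/design sets the schedule: "Data are collected at baseline and 26 weeks, and at 26 weeks post-surgery". Primary outcome measure repeats it for the step count: "This measure will be taken upon entry to the study (test 1), and at approximately 6 months (test 2", with a third measurement 6 months after surgery. Each measurement is one wear period: "Participants will wear an activity monitor (activePAL™) for seven consecutive days". There is one site, so all participants share the same seasons: "The study is conducted in Australia at Launceston, Tasmania".

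Under Data analysis, "Each primary and secondary outcome will be analysed using a two-way repeated-measures analysis of covariance (ANCOVA", and its stated purpose is "to determine differences between groups (exercise versus usual care) and between time points (test 1, test 2 and test 3". The linear mixed model in the same section has condition and time points as its effects. The significance level of 0.05 applies to all analyses. The ANCOVA's covariates are not named, and neither season nor calendar date appears anywhere in the article.

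The hypothesis in Background is a between-group one: the programme "will be more effective than usual care in increasing the number of daily steps at all-time points after intervention". Under Randomisation, "After completing all baseline data collection measures, participants are randomised to either the intervention group or the control group", and under Usual care the controls are assessed on the same schedule.

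**The concern.** Daily walking may vary with weather and daylight. If it does, a gap of half a year is the interval at which the baseline value helps least. Someone who enters at the seasonal low is measured again at the high, and the reverse. The baseline then carries the seasonal component with the opposite sign, which lowers the correlation between tests 1 and 2 and counts season twice in any change score.

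Two separate things are at stake. The first is the precision of the group comparison. The second is the meaning of the time-point test that the plan commits to, where a movement shared by both arms could be seasonal and be reported as a significant change. Which of the two matters depends mainly on how recruitment is spread over the calendar.

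**Working it through.** **Inputs from the protocol.** Test 2 is at 26 weeks; there are 50 per group, a target of 1200 steps (24%), alpha 0.05 and power 0.8 (Sample size).

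**Inputs assumed.** Seasonal half-range A of 300, 600 or 900 steps; correlation r between tests 1 and 2, net of season, of 0.65 (0.50 as a check); the recruitment calendar. None of these is in the document.

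**The plan's own figure.** No SD is stated, so 50 per group cannot be reproduced independently. It can only be solved backwards.
- Normal approximation, two-sided: SD = 1200 × √(50/2) / (1.960 + 0.842) = 6000 / 2.802 ≈ 2142.
- Two-sided t-test: standardised difference 0.566, so SD = 1200 / 0.566 ≈ 2121.

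I use S = 2121 as the SD of a single-visit step count, season included.

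**Phase.** 182 / 365.25 × 360 = 179.4 degrees. The cosine of that angle is −0.9999, so the seasonal component at test 2 is in effect minus that at test 1.

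**Year-round entry: precision of the group comparison.** Season adds v = A²/2 to each visit's variance and −v to the covariance. The observed correlation is r_obs = [r(S² − v) − v] / S². The residual variance of the baseline-adjusted comparison is S²(1 − r_obs²) without a season term and (S² − v)(1 − r²) with one.

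For A = 600:
- v = 180,000; S² = 4,498,641; S² − v = 4,318,641.
- r_obs = (0.65 × 4,318,641 − 180,000) / 4,498,641 = 0.584.
- Without the term: 4,498,641 × (1 − 0.341) ≈ 2,964,000. With it: 4,318,641 × 0.5775 ≈ 2,494,000. Ratio 1.19.
- Equivalent loss of participants: 1 − 1/1.19 = 16%.

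| A | r_obs | Variance ratio, baseline-adjusted | Variance ratio, change score |
|---|---|---|---|
| 300 | 0.634 | 1.05 | 1.06 |
| 600 | 0.584 | 1.19 | 1.24 |
| 900 | 0.501 | 1.42 | 1.57 |

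The change-score ratio is S²(1 − r_obs) / [(S² − v)(1 − r)]. At r = 0.50 the baseline-adjusted ratios are 1.03, 1.12 and 1.27.

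**Power at the planned 1200 steps.** Simulation (3000 trials, 50 per arm, A = 600) gave standard errors of 346 without and 321 with the season term.
- Without: 1200/346 − 1.96 = 1.51, power 0.93.
- With: 1200/321 − 1.96 = 1.78, power 0.96.

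At A = 900 the formula gives standard errors √(3,367,000 × 2/50) = 367 and √(2,364,000 × 2/50) = 307, so power is about 0.90 without and 0.97 with the term. With A = 0 the simulated standard errors were 323 without and 326 with the term, a cost of about 1%.

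**Bias in the group comparison.** A second simulation (2500 trials per setting, SD 2142 before season, correlation 0.6, A of 0, 500 and 750) gave mean estimates of 1190 to 1205 for a true 1200, and type I error of 4.6% to 5.5% without a season term. There is no bias.

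**Short entry: the time comparison.** With entry even over w months centred on the seasonal low, the mean seasonal change from test 1 to test 2 is 2A × sin(πw/12) / (πw/12), the same in both arms.

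| Entry window | Multiple of A | A = 500 | A = 600 |
|---|---|---|---|
| 3 months | 1.80 | 900 | 1080 |
| 6 months | 1.27 | 637 | 764 |
| 9 months | 0.60 | 300 | 360 |
| 12 months | 0 | 0 | 0 |

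In the second simulation with A = 500, a paired test within the control arm declared a change over time in 62% to 65% of trials with 6-month entry, and in 4% to 5% with 12-month entry. For the group comparison at 1200 steps, 6-month entry gave power of 92.3% without and 92.1% with the season term. Twelve-month entry gave 90.6% and 92.7%.

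**The case against.** The strongest reply is that this is an optional refinement. The trial's question is between groups, controls are measured on the same schedule, and randomisation follows baseline, so season cannot favour either arm. The ANCOVA names no covariates at all, and an article may leave that list to the full protocol or analysis plan. The amplitude is assumed, and the middle case is steep: a half-range of 600 is a peak-to-trough swing of 1200 steps, as large as the target effect and 24% of the implied 5000 steps (1200 / 0.24). At 300 the inflation is only 5%. A single site enrolling 110 people, with the intervention run in groups of at most five, is unlikely to take all its baselines in one 3-month low season.

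Most of this stands and sets the weight of the point. What remains is that the half-year interval is fixed, the time-point test is already committed to, and baseline adjustment does not deal with season at this lag. A covariate list held elsewhere would not change how that time-point test is read.

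A reader might infer three stronger things, none of which the document supports:
- **That season biases the treatment effect.** Concurrent randomised controls prevent this.
- **That season necessarily appears as change over time.** With entry spread evenly over whole years the average seasonal change is zero.
- **That both harms occur in full together.** They largely exclude each other: year-round entry inflates group error, while short or uneven entry shifts the time comparison.

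Nor does every participant move from a seasonal extreme to its opposite. With even entry, one third have a seasonal change smaller than half the peak-to-trough range.

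**Conclusion.** The point holds as a conditional one about precision and interpretation. It does not threaten the validity of the primary group comparison. If steps are seasonal and entry is year-round, the baseline-adjusted residual variance at test 2 rises by about 5% to 42% for half-ranges of 300 to 900 steps. The power loss at 1200 steps is modest: about 0.93 against 0.96 at 600, and still about 0.90 at 900. If entry is short or uneven, group precision hardly changes, but the test 1 to test 2 comparison can move in both arms by several hundred steps, and by about 1080 in the extreme case of a 600-step wave and 3-month entry at the low.

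These figures rest on an assumed amplitude, a correlation of 0.65, an SD solved back from the sample size and taken as the SD of a single-visit count, and a single smooth yearly wave. The sign reversal applies to test 2 only. Test 3 is tied to surgery, so its season relative to baseline varies with the length of the wait.

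**What to change.** Make two additions to Data analysis.

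1. In the repeated-measures models for daily steps and sedentary percentage, include the sine and cosine of the day of year of each visit's own wear week as a time-varying covariate. Do not add separate baseline terms: at test 2 they are almost exactly the negatives of the visit's own terms, and so collinear with them.
2. State that the main effect of time and within-arm changes from test 1 to test 2 are descriptive, and that programme effects are read only from between-group contrasts.

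The cost is a few lines of wording and two degrees of freedom. Wear dates come with the monitor data, so nothing new is collected. If there is no seasonality, the standard error rises by about 1%. If recruitment turns out to be short, season and time are nearly collinear and the covariate cannot separate them. In that case only the second statement protects the interpretation, so both should be adopted.

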### Confidentiality

All data collected will be regarded as confidential and securely stored.

### Informed consent

Eligible participants are assessed for inclusion in the study. All participants are asked to provide written informed consent prior to enrolment in the study.

### Ethical and organisational review

Ethical approval for the ENHANCE trial has been granted by the Human Research Ethics Committee (H0016201) at the participating site. The protocol conforms to CONSORT guidelines [39] for reporting non-pharmacological interventions.

## Discussion

The ENHANCE trial is an intervention designed to improve physical activity participation and health-related outcomes in patients on the waiting list for hip or knee arthroplasty. This study is the first of its kind to use a supervised exercise intervention with behavioural counselling based on HAPA to motivate and change behaviours that support increases in physical activity. Findings from this study will add to the growing research literature on essential components for the optimum delivery of exercise for chronic disease management. Furthermore, this study may yield insights to our understanding of the strengths and limitations of a novel behaviour change intervention that is embedded in an exercise programme for people with a chronic disease, using OA as a model for chronic disease. An exercise intervention that can increase overall physical activity levels and improve individuals’ exercise self-regulatory and self-management capacity could be significant in improving the management in the community of people on the waiting list for hip and knee arthroplasty.

### Limitations

The authors acknowledge the following limitations: a single-centre trial, lack of a cost-effectiveness analysis, and limited patient and public involvement in the design of the intervention (Additional file 2).

### Trial status

The trial is currently ongoing.

## Abbreviations

AEP: Accredited exercise physiologist
ANCOVA: Analysis of covariance
ENHANCE: Exercise and behaviour change counselling
HAPA: Health Action Process Approach
HR max: Maximum heart rate
MVC: Maximal voluntary contraction
OA: Osteoarthritis
SF-12: Short Form 12-item health survey on medical outcomes
